**Methods/Design:**

This is a quasi-randomised controlled trial. The intervention period is 12-weeks with 3-month follow-up. The trial will be conducted at a university setting and community health services in South Australia. Participants will be insufficiently active and aged 18 years or older. Participants will be randomly assigned to either the intervention or control group. All participants will receive a pedometer but only the intervention group will have access to the STRIDE website where they will report steps, affect and ratings of perceived exertion (RPE) during exercise daily. Researchers will use these variables to individualise weekly step goals to increase walking.

The primary outcome measure is steps per day. The secondary outcomes are a) health measures (anthropometric and physiological), b) dietary habits (consumption of core foods and non-core foods) and c) quality of life (QOL) including physical, psychological and social wellbeing. Measures will be collected at baseline, post-intervention and 3-month follow-up.

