## Methods/Design

### Participants and setting

The STRIDE study is a quasi-randomised controlled intervention trial. Participants will be allocated to either the intervention group or the wait-list control group. Approximately 80 participants will be recruited and randomised by the research investigator(s). Table 1 shows the inclusion and exclusion criteria.

**Table 1 T1:** Inclusion and exclusion criteria

**Inclusion criteria**	**Exclusion criteria**
• Age over 18 years, no age limit higher	• Patient with metastasis,
• Have had cancer treated with curative intent (excluding skin cancer)	• Pregnant or intending to become pregnant during study period,
• Not undergoing active treatment (including chemotherapy and radiotherapy but will be included if taking long-term follow-up medications or therapies such as hormone therapy)	• Physical or psychological condition (i.e. cognitive decline) that may impede their participant in the study
• Permanent resident of South Australia,	
• Insufficiently active (engaging in less than 20 sessions of physical activity, one session lasting 30 minutes) over the past month determined by The Active Australia Survey [22]	
• Regular access to the internet (whether it be personal access or through a library or community centre)	
• Sufficient English language skills and cognitive ability to complete questionnaires,	
• Satisfy stage one of the pre-exercise screening guidelines for commencing exercise determined by the Sports Medicine Australia Pre-Exercise Screening System [23]	
• Approval by treating doctor to be part of the study,	
• Provide written informed consent	

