### Study design and recruitment procedures

#### *Recruitment and screening*

The study flow is presented in Figure 1. Participants will be recruited via cancer support groups, newspaper advertisements, hospitals, flyers, government departments and allied health personnel contacts. Potential participants will firstly be screened by telephone to determine eligibility, and if eligible will be provided with further study information, a consent form and pre-exercise screening form, and asked to obtain medical clearance from their treating doctor using a standardised medical clearance form. Pre-exercise screening will be conducted using Stage 1 of the Sports Medicine Australia Pre-Exercise Screening System [23]. The first stage of the screening system is designed to screen out those people who are at a high risk for exercise-related complications due to underlying cardiovascular, cerebrovascular, respiratory or metabolic diseases and also pre-existing injuries. Upon completion and receipt of required consent and clearance forms by the research team, participants will be randomised into treatment conditions and contacted to make arrangements for study participation.

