### Randomisation and blinding

Participants will be randomly allocated to one of the two trial arms (intervention or wait-list control). A block design with allocation weight of 3:3 will be used to generate treatment allocation. It is not possible for three key researchers (LF, DZ, RS) to be blinded to participants’ group allocation as they will be performing the information sessions relevant to each group. It is not possible to blind participants to group allocation due to the nature of the intervention. Six other research assistants performing physical and questionnaire measurements will be blinded to the participants’ group allocation.

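### A single stated 3:3 block, with the same investigators recruiting and randomising in an open-label trial, could make up to about a quarter of assignments knowable in advance

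*Protocol article*

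**What the plan says.** Under Randomisation and blinding, the article says allocation to the two arms is random and gives one method: "A block design with allocation weight of 3:3 will be used to generate treatment allocation". No other block size appears.

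Under Participants and setting, enrolment and allocation fall to one role: "Approximately 80 participants will be recruited and randomised by the research investigator(s".

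On blinding, three key researchers know the allocation, "as they will be performing the information sessions relevant to each group". For participants: "It is not possible to blind participants to group allocation due to the nature of the intervention". Outcome measurement is protected: "Six other research assistants performing physical and questionnaire measurements will be blinded".

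On sequence of events, Recruitment and screening begins: "Potential participants will firstly be screened by telephone to determine eligibility". Allocation comes after the paperwork: "Upon completion and receipt of required consent and clearance forms by the research team, participants will be randomised into treatment conditions".

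On the label, the Abstract states: "This is a quasi-randomised controlled trial". Participants and setting repeats that description, although both the Abstract and Randomisation and blinding also say that assignment is random.

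**The concern.** In a block with three places per arm, the remaining assignments are fixed once one arm is full. A person who knows the block size, where each block starts and what has been assigned can then name the next arm with certainty, and can guess better than chance before that point. Here the block pattern is published, assignments are open once made, and whoever randomises necessarily knows the earlier ones. The article gives that task to the role that also recruits.

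The control is a wait-list and the primary outcome, steps per day, is behavioural. Someone able to anticipate the next arm could, deliberately or not, let a more motivated person's forms through now and hold another's back. The primary comparison is a t-test of change scores, for which no covariates are stated. Even an adjusted analysis could not remove selection on traits that were not measured, such as motivation. The blinded assistants guard against biased measurement, not against anticipation at enrolment.

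The label is a separate problem of wording. Quasi-randomised ordinarily means allocation by a non-random, predictable rule. A reader grading the evidence cannot tell which description applies.

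**Working it through.** The article gives no figure for predictability, so there is none to reproduce.

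**Inputs from the article**
- Block pattern 3:3 (Randomisation and blinding), read as a constant block of six.
- Total sample size 82, or 41 per group (Sample size calculation); about 80 (Participants and setting).

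**Assumptions not stated in the article**
- The block size never changes and its boundaries are known.
- Every earlier assignment is known.
- Participants are allocated one after another.

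**Enumeration.** There are C(6,3) = 20 equally likely blocks. An assignment is certain when one arm already has its three places filled.
- Positions 1 to 3: never certain.
- Position 4: the first three must be the same arm, 2/20 = 0.10.
- Position 5: one arm must have filled all its places within the first four, 2 × C(4,3)/20 = 8/20 = 0.40.
- Position 6: always certain, 1.00.

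For best guessing, the rule is to name the arm with more places left and toss a coin when they are equal.

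| Position | Certain in advance | Best guess correct |
|---|---|---|
| 1 | 0 | 0.5 |
| 2 | 0 | 3/5 = 0.6 |
| 3 | 0 | 0.6 × 0.5 + 0.4 × 3/4 = 0.6 |
| 4 | 0.10 | 0.1 × 1 + 0.9 × 2/3 = 0.7 |
| 5 | 0.40 | 0.4 × 1 + 0.6 × 0.5 = 0.7 |
| 6 | 1.00 | 1.0 |
| Sum | 1.5 of 6 = 25% | 4.1 of 6 = 68.3% |

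**Applied to this trial**
- N = 82 is 13 full blocks plus 4. Certain: 13 × 1.5 + 0.1 = 19.6. Correct guesses: 13 × 4.1 + (0.5 + 0.6 + 0.6 + 0.7) = 53.3 + 2.4 = 55.7, or 55.7/82 = 67.9%.
- N = 80 is 13 full blocks plus 2. Certain: 19.5. Correct guesses: 53.3 + 1.1 = 54.4, or 68.0%.

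**How far the 25% depends on knowing the boundaries.** Suppose the recruiter sees only the running difference between arms and treats a difference of three as decisive. Then only position 4 can be certain. With 14 blocks reaching that position, 14 × 0.10/82 = 1.7%. A constant, published block size matters because simple counting then reveals the boundaries.

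**What varied block sizes would do.** In a simulation (20,000 runs, N = 82; sizes 4, 6 and 8 drawn at random, which is an assumption), assignments made certain by the running difference fall to about 0.2%. The comparable figure for fixed sixes is the 1.7% above. Someone tracking the full history could deduce somewhat more: for example, four assignments to one arm among the first five can only come from a block of eight, so the next three are known. Guessing the arm that is behind is still right about 68% of the time. Variation therefore removes most certainty but does not bring guessing down to 50%.

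**The case against.** The strongest reply has four parts.

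- **The article is condensed.** Who holds the list and how assignments are released are details that a full protocol commonly carries, and safeguards may already exist. This stands: silence on concealment is not the finding. The point rests on what is printed, namely one block pattern, open allocation, and one role that recruits and randomises.
- **The figures are a worst case.** The article does not use the words fixed or six, and does not say whether participants are randomised singly or in batches before the workshops. Batching would lower the figures. This also stands, and 25% should be read as an upper figure under the listed assumptions.
- **The opportunity is limited.** Eligibility, consent and the treating doctor's clearance come before allocation, and clearance is partly in outside hands. On the order described, the baseline workshops come after allocation, so recruiters would not yet hold baseline step counts. This narrows the risk. Judgement at telephone screening and the order in which completed forms are handled still rest with the team.
- **Measurement is blinded.** True, but this addresses a different bias.

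Some stronger readings are tempting and unsupported. A reader might infer that the three unblinded researchers are the recruiters; the article does not say so, and the argument does not need it. A reader might infer that selection bias follows; predictability becomes bias only if someone acts on it. A reader might take the quasi-randomised label as evidence that allocation really is non-random; the label only conflicts with the described method. A reader might also object that the blocks are not stratified by region. The article does not say whether they are, and leaving region unstratified would not in itself bias the comparison.

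**Conclusion.** The point holds as a risk created by the stated method. With a constant block of six, known boundaries, known earlier assignments and one-at-a-time allocation, up to about 25% of assignments (about 20 of 82) can be known beforehand, and best guessing would be right about 68% of the time. The 50% expected by chance is not a fair benchmark for what varied blocks alone would achieve. The documents do not show that anyone will act on this knowledge, so no size can be given for any resulting bias in steps per day. Separately, the quasi-randomised label contradicts the random allocation described in the same article. That needs correcting whichever is true, and does not depend on the arithmetic.

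**What to change.** - Generate the sequence by computer with randomly varied block sizes, and do not disclose the sizes to those who recruit.
- Have an existing colleague or an online tool, with no part in screening, enrolling or scheduling, hold the list and release one assignment at a time after eligibility is confirmed. This is the essential step. State it in the article in place of the sentence that joins recruiting with randomising. If such an arrangement already exists, say so.
- Delete quasi-randomised from the Abstract and from Participants and setting. If allocation is in fact not random, keep an accurate label and stop describing the trial as randomised.

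The cost is a new list, a release step and a wording change, with no extra participants or new staff. The downsides are minor logistics and a possible small imbalance from an unfinished last block. If the largest block were eight, the arms could differ by at most 4. Under the present scheme at N = 82, the last four could split 3:1, a difference of 2.

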### Ethical approval

This study has received ethical approval from the University of South Australia Human Research Ethics Committee prior to study commencement and is registered with the Australian New Zealand Clinical Trials Registry (Trial Registration: ACTRN12613000473763).

### Protocol

All participants will attend two baseline workshops, one week apart. Each session will last approximately 90 minutes. At the first workshop, health measures will be taken (blood pressure, weight, height, waist and hip circumference) and fitness will be assessed using the 6-minute walk test. Participants will complete questionnaires about their physical functioning, quality of life and diet habits. They will be provided with a sealed pedometer (New-Lifestyles NL-1000 pedometer, New Lifestyles Inc., Lees Summit, MO) to wear for seven consecutive days (5 week days and 2 weekend days) which they will return at session two. At session two all participants will be provided with lifestyle information and a pedometer for use in the intervention (Yamax Digiwalker SW700). Those in the intervention group will be instructed on using the STRIDE website including how to log their steps and report their RPE and affect each day. On the basis of this information, they will be emailed weekly step goals which they will be encouraged to achieve. Following the 12-weeks of the intervention period, all measures will be repeated, and again after 6-months (i.e. 3-months post-intervention). At the conclusion of 6-months the control group will be offered the STRIDE program.

### Intervention – STRIDE website

The STRIDE intervention involves two key components, the STRIDE website and weekly step goals which participants are encouraged to achieve daily. Participants use a pedometer to monitor the number of steps taken each day, and record their daily steps using the step log on the STRIDE website. In addition to steps taken, participants will report their RPE and affect daily (described below). The step log screen will include a graph of average weekly steps which provides participants with feedback on progress throughout the intervention. There will also be an online forum through which participants can share experiences and provide peer support. Social support has been consistently reported as a predictor of maintained behaviour change in lifestyle promotion [24-28]. A virtual notice board will provide space for community service providers such as community centres, health services and walking groups to advertise events and activities, as well as provide high quality evidence-based guidance on lifestyle behaviours. This feature will be designed to reduce environmental barriers by increasing access to safe, supervised and socially focused opportunities for cancer survivors and family members. The website will also include information on healthy eating based on the Cancer Council Australia’s nutrition guidelines that in turn are based on recommendations in The Australian Guide to Healthy Eating [29].

### Step goals

Personalised step targets will be created using individuals’ RPE and affect. RPE is determined using Borg’s (1998) 6–20 Ratings of Perceived Exertion (RPE) scale [30] that numerically quantifies the effort, strain, discomfort and/or fatigue experienced during physical activity to represent how difficult or easy the activity is perceived to be [30]. RPE has been used to create target exercise intensities in a range of populations including healthy adults [31,32], cardiac patients [33] and patients with chronic obstructive pulmonary disease [34-36]. Researchers have suggested that RPE can be beneficial to elderly or patient populations where direct methods using maximal exertion are considered unsafe [37]. Research has indicated that affective state (feeling good/bad) influences exercise behaviour and motivation [38]. Given that a population such as cancer survivors may experience wide variability in affective state, how the individual is feeling will be taken into account when setting the individualised step goals. Participants will rate their affective state (i.e. how they feel [good or bad]) each day on a scale of +5 (‘Very good’) to -5 (‘Very bad’) [39].

Researchers on the STRIDE research team will use these inputs (daily steps, RPE during walking and daily affect) to generate individually tailored target steps/day for the following week that maintain exertion at between RPE 11 (light) and 13 (somewhat hard) on the RPE scale, the “bandwidth” within which people have the most positive response to exercise [40-42]. Three-tiered step goals will be provided to participants using the affect scale – a goal for when the participant is feeling ‘bad’ (i.e. minus on the affect scale), ‘neutral’ and ‘good’. This method will be employed to ensure that the goals are perceived to be challenging yet achievable, as recommended by Locke and Latham [21], even with variability in affective state from one day to the next. That is, the goals will take into account how the individual feels and be higher when affect is ‘good’ than ‘neutral’ and ‘bad’.

The step goals will be determined from steps, RPE and affect reported in the previous week. If participants do not meet the step goals set for the previous week on most days, the goal for the following week will not change from the previous week. The first week will serve as baseline data on which to set the first goals, with 0%, 5% and 10% increments on average steps achieved set for ‘bad’, neutral’ and ‘good’ days respectively. Weekly goals were set by LF and DZ and confirmed by JD and GP.

### Outcome measures

Outcome measures will be assessed at three time points: baseline, end-program (week 13) and at the 3-month follow-up. The primary outcome is *daily steps*. Participants will wear a sealed pedometer (New-Lifestyles NL-1000 pedometer, New Lifestyles Inc., Lees Summit, MO) for seven consecutive days (5 week days and 2 weekend days), except for sleeping, showering, bathing, swimming or engaging in contact sports. Minimum wear time, as recorded by a log sheet, will be defined as 10 hours per day for four of the seven days, one of which must be a weekend day. The NL series pedometer has extensive empirical backing in the literature for validity and reliability, and displays the accuracy required to detect changes in step counts that are typical of walking interventions [43].

Secondary outcomes include:

#### *Anthropometry*

The following anthropometric measures will be taken: standing stretch stature using a portable stadiometer (SECA, Hamburg, Germany); body weight (Tanita UM-108, Tanita Corporation, China); and waist and hip girths (Executive Thinline 2 m W606pm, Lufkin Tape, Apex, NC). All physical measurements will be taken according to the International Standards for Anthropometric Assessment [44]. A minimum of two measures will be taken at each site. A third measure will be taken if the difference between the first and second measures is greater than 0.5 cm for stature, waist and hip girths.

#### *Physiological measures*

Resting blood pressure will be measured after participants have been seated for five minutes using automated sphygmomanometers (Dinamap Pro 100, GE Medical Systems Information Technologies and Critkon Company, LLC, United Kingdom). Measures will be repeated until there are two readings within 5 mmHg for both systolic and diastolic pressure, up to a maximum of four times.

#### *Diet quality*

A semi-quantitative Dietary Questionnaire for Epidemiological Studies (DQES) developed by the Cancer Council of Victoria [29] will be used to assess change in dietary habits. The DQES asks about food intake over the previous 12 months. It contains 74 items with 10 frequency response options ranging from “Never” to “3 or more times per day”. The questionnaire also contains three photographs of scaled portions of four foods, questions on the overall frequency of fruit and vegetable consumption and questions on consumption of foods that do not fit easily into the frequency format, such as breads.

The 74 food items are grouped into four categories: cereal foods, sweets and snacks; dairy products, meats and fish; fruit; and vegetables. A separate set of questions covers intake of alcoholic beverages. The DQES takes approximately 30–45 minutes to complete. The DQES has been validated in mid-age Australian women [45] and a community sample of young Australian adults [46].

Sweetened drink intake (soft-drink, sports drinks, energy drinks, fruit drinks and cordial) will be measured using a separate three-item questionnaire as sweetened drink intake is not measured in the Cancer Council DQES. For each sweetened drink participants indicate how often, on average, they consumed the drink in the previous 12 months on a 10-point scale ranging from never to three or more times per day, and how much they usually consume on a 3-point scale comprised of one glass (250 ml), one can (375 ml) or one bottle (600 ml).

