#### *Analytic plan*

Data will be entered and analysed using the IBM SPSS version 21 (SPSS, Inc, Chacago, IL) statistical software package. The intent-to-treat principle will be applied and the significance level will be set at 0.05. Baseline comparisons of demographic outcomes will be performed using independent samples t-tests. The primary outcome (number of steps/day) will be reported as independent samples t-tests comparing change scores in the two randomisation groups. Change scores for the secondary outcomes (health measures, diet quality and quality of life) will be calculated for each variable and compared between treatment and control groups using parametric or non-parametric procedures as appropriate for the data distributions.

Random effects mixed modelling will be used with time (0, 12, and 24 weeks) and group allocation (Intervention, Control) as the fixed factors. A time by group interaction term will be used to formally test the aims of the study.

Time by region (rural versus metropolitan) repeated measures ANOVA will be used to examine differences in the primary and secondary outcomes between groups over time. Sociodemographic factors and diet will be controlled for in the analysis.

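### Diet change at about 3 and 6 months is measured with 12-month recall, so roughly three quarters, then about half, of the recalled period predates the intervention

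*Protocol article*

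**What the plan says.** The Diet quality section of the Protocol article gives the DQES a longitudinal purpose: it "will be used to assess change in dietary habits". The next sentence fixes its window: "The DQES asks about food intake over the previous 12 months". A separate three-item questionnaire covers sweetened drinks. For each drink, participants report how often, on average, "they consumed the drink in the previous 12 months on a 10-point scale", and then the usual amount on a 3-point scale. No recall window is stated for the amount question.

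The schedule is in the Outcome measures section: "Outcome measures will be assessed at three time points: baseline, end-program (week 13) and at the 3-month follow-up". The Protocol section repeats all measures after the 12-week programme and again at 6 months. The Analytic plan codes the visits as 0, 12 and 24 weeks.

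The Abstract lists dietary habits among the secondary outcomes. The Analytic plan compares them between arms as change: "Change scores for the secondary outcomes (health measures, diet quality and quality of life) will be calculated for each variable". Nothing in the article shortens the recall period at the later visits or mentions that the recalled periods overlap.

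**The concern.** A change score is informative when the two measurements describe different periods. Here the baseline questionnaire describes the year before the trial, and the end-of-programme questionnaire describes a year of which only the last 12 or 13 weeks follow baseline. The two recalled years largely coincide, so much of any real change is averaged away by the question itself. No later analysis can recover it.

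The website carries healthy-eating information, so the trial is in a position to ask whether diet moved. If it did move, the planned comparison may well show little. The risk is that a null result, above all at end of programme, is reported as no effect on diet when the instrument had little chance of showing one.

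**Working it through.** The plan gives no attenuation figure, so there is none to reproduce.

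**Inputs**
- Recall window: 12 months, taken as 52 weeks (Diet quality; DQES and drink frequency items).
- End of programme: week 12 (Analytic plan) or week 13 (Outcome measures).
- Follow-up: week 24 (Analytic plan) or 6 months, taken as 26 weeks (Protocol section).
- For the power illustration: 41 per arm and alpha 0.05 (Sample size calculation). Two-sided testing is assumed, as the article does not state it.
- True standardised diet effect d: not given in the article. Assumed range 0.5 to 0.8.

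**Step 1: share of the window on each side of baseline.** After baseline = t/52; before baseline = 1 − t/52.

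| Visit | After baseline | Before baseline |
|---|---|---|
| Week 12 | 12/52 = 23% | 77% |
| Week 13 | 13/52 = 25% | 75% |
| Week 24 | 24/52 = 46% | 54% |
| Week 26 | 26/52 = 50% | 50% |

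**Step 2: expected size of the measured change.** If respondents average over the whole window and diet shifts by D at baseline and stays there, the measured change is D × t/52: 23–25% of D at end of programme and 46–50% at follow-up.

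**Step 3: other time courses.**
- If the shift builds up evenly from zero at baseline to D at week 12, its mean over those weeks is D/2, and the week-12 score shows (D/2) × 12/52 = 0.115 D, about 12%.
- If the shift is D during the 12-week programme and then disappears, the follow-up score shows D × 12/52 = 23% of it. That is a residue of the programme period rather than current diet.
- If respondents weight recent weeks more than the items ask, the measured share is larger than in step 2, by an amount that the article gives no means of estimating.

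**Step 4: illustrative power.** Normal approximation: power = Φ(δ√(n/2) − 1.96), with δ = d × t/52 and an unchanged SD. With n = 41, √(n/2) = 4.528. Example: d = 0.5 at week 24 gives δ = 0.231, so Φ(1.045 − 1.96) = 18%.

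| Assumed d | Undiluted | Week 12 | Week 13 | Week 24 | Week 26 |
|---|---|---|---|---|---|
| 0.5 | 62% | 7.5% | 8% | 18% | 20% |
| 0.6 | 78% | 9% | 10% | 24% | 27% |
| 0.8 | 95% | 13% | 15% | 39% | 44% |

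Applying the article's 20% dropout (41 × 0.8 ≈ 33 per arm), the range for d = 0.5 to 0.8 is 53–90% undiluted, 7–11% at week 12 and 15–32% at week 24.

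**Step 5: with a shorter window.** If the reference period is 12 weeks or less, none of it predates baseline at either later visit, and the factor t/52 is replaced by 1 for a change that is complete at baseline.

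**The case against.** Proportional attenuation is a model. It needs literal 12-month averaging, an immediate and lasting change and an unchanged SD. Respondents may describe recent habits instead, in which case the loss is smaller. How the DQES responds to short-term change would have to come from the validation studies it cites, which are not shown. This stands: the percentages in step 2 are conditional and cannot serve as a correction factor. It does not remove the problem, because a score that depends on how far each respondent departs from the question asked has unknown sensitivity. Participants are also unblinded, so that departure could differ between arms.

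A reader might infer that most of the window predates the intervention at both visits, or that the instruments cannot show a diet change at all. The documents do not support either. At follow-up the share before baseline is 54% or exactly half, and about half of a sustained change should still appear.

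A reader might also treat the whole drink questionnaire as 12-month recall. Only the frequency items state that window; the usual-amount question does not, and could shift at once.

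The power figures rest on an effect size that the article never gives for diet, and all participants receive lifestyle information at the second baseline workshop, so a between-arm effect of that size is not established. They are illustration only. Finally, diet is one of three groups of secondary outcomes, and under averaging the error runs towards the null, so a false claim of benefit is not the main risk.

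**Conclusion.** The concern holds for the DQES and for the sweetened-drink frequency items. The stated recall window does not fit the stated purpose of measuring change over about 3 and 6 months. The overlap follows directly from the article: 75–77% of the window precedes the intervention at end of programme and 50–54% at follow-up. The attenuation to 23–25% and 46–50% of the true change is conditional on averaging as asked and on a full, lasting change from baseline. The power loss further depends on an assumed d and an unchanged SD.

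It would be tempting to read the follow-up result as about half of the true change and scale it up. That is not supported, because the fraction depends on recall behaviour and on the time course, neither of which is known.

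The consequence is confined to interpreting the diet outcome. Steps per day come from a pedometer and are not measured by these questionnaires. The Analytic plan also says that diet will be controlled for, so a score that lags behind current diet could enter those models if a post-baseline value is used. The point should be corrected, but it does not threaten the primary comparison.

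**What to change.** Set the reference period of the sweetened-drink frequency items to one that fits between visits, for example the past month and at most the past 12 weeks. Use it identically in both arms and at baseline, end of programme and follow-up. The article cites no validation for these items in their 12-month form, so the cost is a wording change.

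Give the same reference-period instruction for the DQES where it can be altered. The cost is that the cited validation, and any outside norms, apply to the 12-month form of an instrument developed by a third party. The between-arm comparison is preserved as long as the wording is the same for everyone at every visit.

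If the DQES cannot be altered, treat its end-of-programme comparison as exploratory. State that DQES change is attenuated by an unknown amount at both later visits, so that a null result is not evidence of no diet effect. Do not report a fixed correction. The Step goals section describes part of goal setting in the past tense, so baseline questionnaires may already have been collected. For participants whose baseline used the 12-month form, a mid-trial switch would break the change score, and the same limitation statement should then apply to the drink frequency items.
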